#### Quantitative Survey Data

Descriptive statistics will first be conducted on all variables to identify methodological data trends and parameters. We will analyze differences in baseline demographic and clinical variables using Pearson chi-square and nonparametric Wilcoxon rank sum tests. Given that we will be asking the same patients to complete repeated outcome measures across 4 time periods, we will account for autocorrelation effects through the use of linear generalized estimating equations, which are a multivariate analog of linear regression for longitudinal data and recommended for use in longitudinal repeated-measures data analyses [65,66]. Our data analysis strategy to answer the following questions is as follows:

(1) What is the effect of Ned on health-related outcomes over time? To assess the effect of Ned on quality of life, satisfaction with cancer care, unmet needs, self-efficacy, and prostate cancer-related level of anxiety domains, we will use generalized estimating equation models containing indicators for each study time point to assess whether the average study assessment scores at 2 months, 6 months, and 12 months were significantly different from baseline values.

(2) Is there a relationship between patient engagement with Ned and changes in health-related outcomes over time? We will explore whether patients who engage with the content and functionality of the app experience improvements in their health and well-being by building linear regression models for use and outcomes data.

(3) Is there a relationship between health-related outcomes? To understand whether changes in health-related outcomes share a similar direction and magnitude, we will perform Pearson correlation analyses to test for a correlational relationship between outcome variables.

(4) Do demographic and clinical variables affect changes in health-related outcomes? We will first conduct independent *t* tests and 1-way independent analyses of variance to determine whether there were differences in health-related outcomes for all categorical demographic and clinical variables, and Pearson correlation analyses for all continuous variables. We will then perform multiple linear regression analyses with health-related outcomes as dependent variables and all significant predictor variables from our preliminary analyses as independent variables.

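### Questions 2 and 4 leave the planned GEE for one-record-per-man tests, which are valid on a change score but ignore the intermediate visits and drop men without the chosen visit

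*Protocol article*

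**What the plan says.** The opening paragraph of Quantitative Survey Data (Methods, Data Analysis) gives the reason for a longitudinal method, "Given that we will be asking the same patients to complete repeated outcome measures across 4 time periods", and names the remedy: "we will account for autocorrelation effects through the use of linear generalized estimating equations". Four questions follow, each with its own method.

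- Question 1 (effect of Ned over time): GEE with an indicator for each time point.
- Question 2 (engagement and changes over time): to be explored "by building linear regression models for use and outcomes data".
- Question 3 (relations between outcomes): "To understand whether changes in health-related outcomes share a similar direction and magnitude, we will perform Pearson correlation analyses".
- Question 4, which asks "Do demographic and clinical variables affect changes in health-related outcomes": independent t tests and "1-way independent analyses of variance to determine whether there were differences in health-related outcomes for all categorical demographic and clinical variables", with Pearson correlations for continuous variables. Then: "We will then perform multiple linear regression analyses with health-related outcomes as dependent variables".

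Table 2 schedules EPIC-26, satisfaction, needs, self-efficacy and anxiety at baseline, 2, 6 and 12 months. The section does not say which visit or change score enters Questions 2 to 4, or how many rows each man contributes.

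**The concern.** The plan identifies the repeated-measures problem, solves it for one question, and then names methods for the others that assume one independent observation per man. Four scores must become one before those methods apply.

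If one change score is used, the scores at the unused visits do not contribute and men lacking the chosen visit are lost. A single change also cannot show when an association appears, although Question 2 asks about change over time and the Introduction lists for whom and over what duration among the study's aims. If the rows were stacked instead, standard errors for predictors fixed per man, such as treatment group or stage, would be too small.

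Questions 2 and 4 carry the dose-response and for-whom findings that feed the context-mechanism-outcome configurations. Question 4 also passes its significant first-step predictors into the final regression, so an error in the first step would carry forward.

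**Working it through.** **Inputs.** From the protocol: four time points (Table 2); six treatment groups (Effectiveness of Ned); 400 recruited, 317 required, 20% dropout, 2-sided 5% (Sample Size). The 5% level is stated only for the sample size and is borrowed here as the nominal level. The within-man correlation ρ is not given, so 0.3, 0.5 and 0.7 are assumed, exchangeable across visits.

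**The plan's own figures.** The protocol states no error rate or precision for Questions 2 to 4. Its dropout allowance does reproduce: 317/(1 − 0.20) = 396.25, so 397, rounded up to 400.

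**Reading A: one change score per man**

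1. *Error rate.* Simulation with 320 men (400 × 0.80) and 4,000 runs, using the 12-month change from baseline in a two-group t test, a six-group ANOVA and a Pearson correlation, rejects in 4.2–5.4% of runs across ρ = 0.3–0.7. There is no inflation.
2. *Precision.* With score variance σ², the variance of the 12-month change is 2σ²(1 − ρ). The variance of the mean of three follow-ups minus baseline is (1 + 1/3)σ²(1 − ρ). Relative efficiency is (4/3)/2 = 0.67, and ρ cancels. This assumes the same predictor effect at each follow-up. If only the 12-month change is of interest and data are complete, the middle visits add little or nothing.
3. *Retention.* 0.20 × 400 = 80 men at the planned dropout. This is a ceiling on what a longitudinal model could recover, because some of these men will lack the earlier visits too.

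**Reading B: visits stacked as independent records**

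For m rows per man and a single predictor fixed per man, the design effect is DE = 1 + (m − 1)ρ, and actual error = 2[1 − Φ(1.96/√DE)]. With m = 4 and ρ = 0.5: DE = 2.5, 1.96/1.581 = 1.240, error 21.5%. For Question 3 both variables change by visit, so DE = 1 + (m − 1)ρ². At ρ = 0.5 this is 1.75, giving 13.8%. The six-group ANOVA was simulated.

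| ρ (assumed) | Single predictor, four scores | Six-group ANOVA, four scores | Question 3 Pearson, four scores |
|---|---|---|---|
| 0.3 | 15.5% | 34% | 8.2% |
| 0.5 | 21.5% | 50% | 13.8% |
| 0.7 | 26.6% | 63% | 21.2% |

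Simulated t tests agree with the first column: 16.1%, 21.2% and 26.8%. If three change scores sharing a baseline were stacked, their mutual correlation is 0.5 whatever ρ is. Then DE = 2 and the error is 16.6% for a single predictor, about 36–37% for the six-group ANOVA (simulated) and about 11% for Question 3.

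**The case against.** The best defence has four parts.

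- **The GEE sentence comes before all four questions.** It can be read as covering them all, and it presents GEE as the longitudinal counterpart of linear regression. This counts against the stacked reading. It does not extend GEE to Question 4, because an independent t test or one-way ANOVA is not a GEE, and Question 2 names plain linear regression.
- **The questions concern changes.** Questions 2, 3 and 4 are all posed about changes, and Sample Size frames the comparison as baseline to study conclusion. One change score per man is therefore the natural reading, and the named tests are then correct. This stands. Preferring a longitudinal model is then a matter of precision and retention, not validity.
- **An article may leave the choice of visit to a fuller plan.** This also stands, and the missing visit definition is not held against the protocol. What remains is a method choice that the article does state: GEE for one question, independence-based methods for the others.
- **These analyses are partly exploratory.** Question 2 says it will explore, and results are triangulated with qualitative data. This lowers the weight of the point but does not remove it.

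Question 3 needs little change. Pearson correlations of change scores suit its stated aim; only the one-record-per-man condition needs stating.

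**Conclusion.** The point holds as an improvement to the analysis of Questions 2 and 4, not as a finding that the planned tests are invalid. On the natural reading the tests keep their 5% level. The cost is an efficiency of about 67% relative to averaging three follow-ups (exchangeable correlation, constant effect) and the exclusion of at most about 80 of 400 men at the planned dropout.

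A reader might infer two stronger conclusions, and the documents support neither.

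- *That false positives in Questions 2 to 4 will run at 17–22%.* The protocol nowhere plans to stack visits. That range is three stacked changes (16.6%) to four stacked scores (21.5%) at an assumed correlation of 0.5, and it fits only a single predictor fixed per man. It is too low for a six-group ANOVA and too high for Question 3.
- *That half the data are lost.* Two of four visits go unused, but that counts visits, not information. The efficiency loss is about one third under a constant effect, and little or nothing for a purely 12-month target with complete data.

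**What to change.** Answer Questions 2 and 4 in the Question 1 GEE: add the predictor (engagement, or the demographic or clinical variable) and its interaction with visit, with robust standard errors clustered on patient. The predictor-by-visit terms estimate how change from baseline differs with the predictor at 2, 6 and 12 months. Men who miss 12 months still contribute their earlier scores, and stacking as independent rows is ruled out. For Question 3, keep the Pearson correlations but state that they use change scores, one record per man, computed separately at each follow-up visit and not pooled.

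The cost is slightly more model code and more coefficients to report. No new data are needed. GEE uses the available visits but does not by itself remove bias if dropout depends on the outcome.

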### Sample Size

The appropriate sample size for single-case research depends on the specific research question being investigated and cannot be calculated in the same way as group designs such as the randomized controlled trial. In his seminal writing on case study designs, Yin recommends abandoning traditional sampling logic in favor of reflecting on the number of replications that are desired to maximize both certainty of research findings and external validity [59]. However, we recognize that our study design diverges from traditional case study methodology in nesting a within-group pre-post comparison of health outcomes aimed at identifying possible parameters of clinical change from baseline to study conclusion. We have therefore diverged from Yin’s recommendations and performed a sample size calculation powered to detect a minimal clinically important difference (MCID) of 4 with a standard deviation of 22.25 on the EPIC-26. We selected the most conservative MCID and the median standard deviation from the range of validated values (MCID range 4-12, SD range 12.6-31.9), which have been widely used in prostate cancer survivorship research [60]. With 90% power, an effect size of Cohen *d*=0.16, and a 2-sided significance level of 5%, a minimum of 317 participants are required to detect this MCID. We anticipate a dropout rate of 20%, bringing our total sample size to 400 prostate cancer survivors for recruitment. We performed this calculation using the G*Power 3.1 software [61]. We will actively recruit the 400 patients required to power our within-group pre-post comparison of health outcomes, but we do not have a predetermined sample size for caregivers and clinicians. We anticipate that 10 clinicians will accept the invitation to join the Ned study and 50% of patients will share Ned with their caregivers. This will result in a total study sample size of 610 participants, composed of 400 patients, 200 caregivers, and 10 clinicians.

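### Question 4 asks about changes in outcomes but does not tie its tests to change, and it selects predictors by significance on the same data that then test them

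*Protocol article*

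**What the plan says.** Protocol article, Data Analysis, Quantitative Survey Data, sets out four questions after stating that repeated measures will be handled by linear generalized estimating equations (GEE). Question 1 uses GEE with an indicator for each time point and compares 2, 6 and 12 months explicitly with baseline.

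Question 4 reads "Do demographic and clinical variables affect changes in health-related outcomes". Its first step is independent t tests and one-way analyses of variance "to determine whether there were differences in health-related outcomes for all categorical demographic and clinical variables", with Pearson correlations for continuous variables. Its second step is "multiple linear regression analyses with health-related outcomes as dependent variables and all significant predictor variables from our preliminary analyses as independent variables". Question 4 names no change score, baseline term, predictor-by-time term or time point.

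Question 3 gives as its purpose whether changes in outcomes share direction and magnitude, and then says "we will perform Pearson correlation analyses to test for a correlational relationship between outcome variables".

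The clinical variables collected (Effectiveness of Ned) are Gleason score, stage, treatment group and comorbidities. The demographic variables are not listed.

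**The concern.** There are two separate problems in Question 4.

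First, the question is about change, but the analyses are written on the outcomes themselves. The treatment groups range from active surveillance to castration-resistant disease, and the EPIC-26 scores urinary, sexual, bowel and hormonal function. Eligibility sets no treatment type or time since treatment. Such groups can plausibly start at different levels. If follow-up scores are compared without reference to baseline, a difference that was there on day one is read as a difference in how patients changed.

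Second, the final regression admits only predictors that were significant in the preliminary tests. The same data choose the predictors and then test them, so the final P values do not have their nominal meaning. A real confounder that misses significance on its own never enters the model.

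For whom Ned works is part of the evaluation's defining question (Innovative mHealth Clinical Trials), and the quantitative results feed the realist program theory, so the answer to Question 4 matters beyond a footnote.

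**Working it through.** The protocol gives no figure for Question 4, so there is none to reproduce. The checks size the two mechanisms.

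**Inputs from the protocol (Sample Size).** The calculation is for a "minimal clinically important difference (MCID) of 4 with a standard deviation of 22.25 on the EPIC-26". The test is two-sided at 5%. This level is stated for the sample size only; no screening threshold is given, so 5% is assumed for the screen. Completers: 400 × (1 − 0.20) = 320.

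**Assumed inputs.** Two equal groups of 160; a constant gap of 4, 5, 8 or 10 points at baseline and follow-up; baseline-to-follow-up correlation 0.5 or 0.7; 4, 8 or 12 independent candidate predictors with no true effect.

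**1. Follow-up scores against change scores.** Standard error of the group difference = 22.25 × √(2/160) = 2.49. Rejection rate ≈ Φ(gap/2.49 − 1.96):

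| Gap | gap/SE | Rejection on follow-up scores |
|---|---|---|
| 4 | 1.61 | 0.36 |
| 5 | 2.01 | 0.52 |
| 8 | 3.22 | 0.89 |
| 10 | 4.02 | 0.98 |

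Simulated t tests agree: 36%, 52%, 89% and 98% at correlation 0.5. The true difference in change is zero in every row, and the simulated test on change rejects in about 4% to 5%.

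**2. Screening on significance.** For k independent null candidates, the chance that at least one passes is 1 − 0.95^k per outcome:

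- k = 4: 1 − 0.95^4 = 18.5%
- k = 8: 1 − 0.95^8 = 33.7%
- k = 12: 1 − 0.95^12 = 46.0%

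Across the five outcome constructs, if independent, the exponents become 20, 40 and 60, giving 64%, 87% and 95%.

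In a simulation with 8 null predictors and 320 patients, 95% of those that passed the screen were again significant in the final regression, and 33% of analyses ended with at least one significant predictor. This is expected: when a single continuous predictor passes, its regression P value is the same as its correlation P value, so the second step adds no independent check.

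**3. A remedy that does not work.** Regressing the 12-month score on the baseline score plus covariates may look like an alternative way to analyse change. With pre-existing groups that differ at baseline it is not equivalent. For an 8-point gap, correlation 0.5 and identical change, the expected group coefficient is 8 − 0.5 × 8 = 4 points. Its standard error is about 22.25 × √(1 − 0.25) × √(2/160) = 2.15, so rejection is about Φ(4/2.15 − 1.96), roughly 45% (44% simulated). At correlation 0.7 the spurious effect is 8 − 0.7 × 8 = 2.4 points, with 27% rejection in simulation.

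**The case against.** The best defence is that Question 4's opening sentence governs what follows, so the health-related outcomes in the tests may be shorthand for changes in them. This is a condensed article, and the exact derivation of a dependent variable is commonly left to an analysis plan. That much stands. A reader might infer that the protocol plans to analyse outcome levels at 12 months, but it says neither levels nor 12 months for this question. The supportable statement is that the dependent variable is not tied to change. Against the defence, Question 1 in the same section names the baseline contrast when one is meant, and Question 4 does not. The defence does not reach the significance screen at all, because the screen is stated outright and is faulty whichever outcome is meant.

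Three other strong readings are not supported:

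- **Repeated measures ignored.** The section introduces GEE before listing the four questions, and a test on one change score per patient would leave no within-patient correlation to handle.
- **Question 3 has the same fault.** Its rationale already speaks of changes, so the correlated variables are most naturally changes. Only the wording of the test is loose.
- **Baseline gaps and chance findings will be reported as who benefits.** The protocol does not say Question 4 results will be presented that way, and it combines quantitative with qualitative data to build its theory. With no control group, even correctly analysed change shows only who changed.

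**Conclusion.** The point holds in two parts of different strength.

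The significance screen is explicit and should go on any reading. Assuming 4 to 12 independent null candidates and a 5% threshold, 19% to 46% of analyses per outcome admit at least one chance predictor, which almost always stays significant. Correlated candidates or a different threshold would alter these figures.

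The mismatch between question and test is one of specification: the question says change and the tests do not. Its effect depends on how the tests are finally run and on baseline gaps the protocol does not give. If follow-up scores are analysed unadjusted, false-positive rates for change run from about 36% (4-point gap) to 98% (10-point gap) under the two-group assumption. If change scores are analysed, the rate is about 5% and this part is resolved.

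Neither part affects the Question 1 comparison with baseline. It is a correction that should be made before analysis.

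**What to change.** For Question 4:

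- Add covariate-by-time terms to the Question 1 GEE model, or name change from baseline at a stated time point as the dependent variable. Do not offer the baseline-adjusted 12-month regression as equivalent.
- Prespecify the list of collected demographic and clinical variables, including Gleason score, stage, treatment group and comorbidities, and enter all of them. Drop the significance screen.
- Report every term with its confidence interval.
- Label the results as exploratory evidence of who changed, not who benefited, because there is no control group.

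For Question 3, as a minor wording point, state that the correlations are between change scores, in line with its stated purpose.

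Table 2 schedules the Prostate Cancer-Related Quality of Life Scales at baseline only, so those scales cannot serve as a change outcome in either question.

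The cost is analysis-section wording. No new data are needed.

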## Results

We recruited our first survivor in October 2017 and expect to reach our sample size requirements by March 2018. The anticipated completion date for this work is May 2019, and we aim to disseminate study findings through peer-reviewed publications and presentations starting September 2019.

## Discussion

While there is mounting evidence to support the provision of digital prostate cancer survivorship care [18-22], there has not yet, to our knowledge, been an integrated effort to combine care strategies into a single platform for access by patients and their circle of care. Clinical researchers have not yet developed or comprehensively investigated digital interventions capable of eliciting the personal and medical context required to provide appropriate survivorship care. Further, with few exceptions [21,67-69], most existing studies for evaluating digital prostate cancer survivorship resources have been primarily formative in scope and have focused on nascent Web-based technologies [20,70-73]. This leaves a gap in the literature for evaluative research to build on this foundation of knowledge and advance a realist understanding of how to adopt and implement digital prostate cancer survivorship solutions across diverse contexts.

We have endeavored to design an evaluation that can respectfully explore the nuanced relationship between prostate cancer survivors and a technology designed to improve their survivorship care. To our knowledge, this is the first realist case study evaluation of an mHealth platform for prostate cancer survivorship care. The case study design employed for this work is supported by a mixed-methods approach to data collection [59], a strong theoretical grounding in realist principles [33], a pragmatic data collection schedule that aligns with existing implementation timelines [74], and a shared focus between observational and experimental investigation [75]. We have made efforts to select study instruments that are thoughtful in their wording and specific to prostate cancer survivorship, so that patients will understand the relevance of what is being asked of them. Our inclusion of caregiver interviews as both a distinct exploration into the health and well-being of partners and also a complement to the patient survivorship experience is more comprehensive than focusing on survivors alone.

It is acknowledged that most men with a diagnosis of prostate cancer will die *with* it, not *of* it [76-78]; therefore, prostate cancer is a chronic condition that requires effective management. We posit that Ned has the potential to support this management through the systematic monitoring of outcomes and may contribute to a measurable and meaningful shift in health and well-being. The lives of prostate cancer survivors are marked by unresolved needs that are not often addressed through their interactions with their circle of care [79]. We are hopeful that by providing survivors, caregivers, and clinicians with a foundation of shared health information, Ned will initiate informed conversations around the provision and acceptance of empathetic care.

Prostate cancer survivorship care will be at the forefront of health care resource allocation by 2030. Prostate cancer survivors are set to increase in number and longevity, heightening the need for integrated survivorship solutions to provide them with optimal and durable outcomes. We believe that Ned marks the proactive start of a shift in prostate cancer care innovation. We aim for this research to explore the app’s potential to empower the survivorship experience and inform a new era of prostate cancer survivorship care.

